### 2.5. Sample Size and Recruitment

The sample size was calculated using PROC POWER in SAS for a two-sided Score test in the Cox proportional hazard regression of the time to diagnosis of an HDP in the study group, with a binary variable taking on the values of intervention (digital platform plus RBPM) or active comparison (digital platform). The proportion of total participants in the intervention group was set at 50%. A hazard ratio of 1.4 for the study group was used as the effect size. The overall probability that a participant would be diagnosed with an HPD was set at 15.9% [43]. The total number of subjects needed to achieve a power of 80% with a significance level of 0.05 was determined to be 1745. 

Overall, HDP affects 15.9% of delivery hospitalizations in the US [43], and the prevalence is higher among patients served by the study site. In 24 months, our system provides prenatal care to over 3000 patients. Given this patient volume and prevalence, we considered the estimated sample size feasible with a 60% enrollment rate, which is consistent with the engagement with prior research studies in our setting of similar durations. We anticipate that the required cohort for each research objective will be enrolled within the desired timeline. The total active participant enrollment time for the planned protocol will be a total of 48 months: 24 months for phase 1, and 24 months for phase 2. 

All people presenting at the study site for prenatal care will be invited to participate at their initial prenatal visit by a study research coordinator. Individuals younger than 18 years will be excluded. Over 35% of patients receiving prenatal care at our facility identify as Black, which will allow us to test for the desired sub-group effects related to social identification. Randomization will occur at the time of enrollment, and baseline measures will be completed. Participants will receive USD 25 at the time of enrollment and each time they complete study data collection (enrollment, and then each subsequent trimester and postpartum) in recognition of the additional time required to complete these study materials. Survey data will be compiled using REDcap 14.2.1, a software distributed by Vanderbilt University in Nashville, Tennessee, United States, for non-commercial secure survey data collection, at enrollment and the subsequent timepoints.

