### 2.3. Planned Analysis: Time to Diagnosis of Hypertensive Disorders of Pregnancy

A planned analysis will be conducted, with the aim of completing the research objectives, sequentially in two phases. The first research objective will be completed as phase 1 using a time-to-event strategy and intent to treat. In this phase, we will evaluate the days to diagnosis of HDP when using the digital platform, with an active comparison group. The comparison group will receive a digital platform that offers educational content but not RBPM. Patients will be assigned 1:1 using a random number generator to either the intervention (digital platform plus RBPM) or active comparison (digital platform). The hypotheses are the following:Diagnosis of previously unrecognized chronic hypertension will increase with use of RBPM.RPBM and use of the digital platform will decrease the days to diagnosis of HDP.RBPM will decrease the time to diagnosis for all users regardless of demographic characteristics.

When phase 1 is completed, our team will incorporate culturally responsive social identification strategies to increase the engagement among Black patients. The content for cultural tailoring will be developed during phase 1 under a separate protocol not described here. The second research objective will be achieved by evaluating this tailoring in a randomized controlled trial as a second phase. The hypotheses are the following: Cultural tailoring will promote social identification and mediate treatment effects on the time to diagnosis of HDP among Black users, narrowing the equity gap in outcomes.Cultural tailoring will improve the perceived quality of care, reduce stress, and improve social support. These benefits will result in additional improvements in perinatal outcomes, such as fewer preterm birth and depression symptoms.

We further anticipate that social identification will create a consistent “brand” for the program (common desirable features, consistent imagery, look and feel) and will affect the time to diagnosis of HDP outcomes [38]. Recognition of the intervention and its tailored features will promote engagement and participation.

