### 2.4. Outcome Measures

The planned primary outcome is the time to diagnosis of HDP. Planned secondary outcomes include an improvement in the perceived quality of care and reduced maternal stress. Additionally, we will measure the effect of cultural tailoring and its associated impact on health equity. While this study is not powered to detect differences in the rates of severe maternal morbidity, we will evaluate this outcome as an investigational hypothesis. 

We have selected biometric, behavioral, and social identification measures that are linked to our conceptual framework and hypotheses. EHR review will provide information on the diagnosis and timing, gestational age at delivery, mode of delivery, maternal comorbidities, and participation in postpartum care. The study instruments will be applied after consent and before enrollment, during pregnancy as specified, and at six to eight postpartum.

Blood pressure. Blood pressure will be taken using the internet-enabled blood pressure equipment provided, which will be linked to the digital platform and integrated with the EHR. These devices are calibrated and tested for consistency with hospital-based medical equipment. All recorded values will be included from the first prenatal visit to 8 weeks postpartum for research objectives 1 and 2. 

Laboratory values. The results of laboratory testing used to diagnose preeclampsia will be extracted from the EHR, including the complete metabolic panel, urine protein–creatinine ratio, and other data for research objectives 1 and 2. 

Quality of Prenatal Care Questionnaire [39]. The QPCQ is a reliable and validated instrument developed to assess the perceived quality of prenatal care. Reported Cronbach’s alpha = 0.96 and inter-item correlation coefficient = 0.88. This will be completed once each trimester for research objectives 1 and 2. 

Perceived Prenatal Maternal Stress Scale (PPNMSS). This validated instrument consists of 28 items organized as four sub-scales of perceived social support, pregnancy-specific concerns, intimate partner interaction, and economic matters [40]. Cronbach’s alpha = 0.83, with an inter-item correlation coefficient of <0.9. For research objectives 1 and 2, the PPNMSS will be completed once each trimester. 

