##### Objective 1.A and Analysis Plan

The primary outcome will be the days to diagnosis of an HDP, where an HDP is defined as gestational hypertension, preeclampsia, or preeclampsia with severe features. The days to diagnosis of an HDP will be calculated from the date of the first prenatal visit to the date of diagnosis (ICD-10-CM), clinical problem list (SNOMED-CT), and Intelligent Medical Objects (diagnosis and problems). A patient will be considered censored if they are never diagnosed with an HDP. A Cox proportional hazards regression will be used to model the effect of using the digital platform plus RBPM (intervention) compared to the digital platform alone (active comparison) on the days to HDP diagnosis. The regression coefficients and respective *p*-values, and the hazard ratios with confidence intervals will be reported. The predicted survival curves for each group will be plotted, along with the median days to diagnosis for each group. 

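### The hazard ratio of 1.4 behind the 80% power implies about 13.5% v 18.3% of women diagnosed with HDP; if RBPM mainly brings the same diagnoses forward, the primary Cox test has far less power, and a hazard ratio above 1 need not mean earlier diagnosis

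*Protocol article*

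**What the plan says.** All places are in the protocol article.

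- **Hypothesis (2.3).** "RPBM and use of the digital platform will decrease the days to diagnosis of HDP". In the same list, an increase in diagnoses is predicted only for previously unrecognised chronic hypertension. That condition has its own logistic model (Objective 1.B) and lies outside the primary HDP definition (Objective 1.A).
- **Sample size (2.5).** The calculation is for a "two-sided Score test in the Cox proportional hazard regression". On allocation, the article says: "The proportion of total participants in the intervention group was set at 50" percent. On the effect size, it says: "A hazard ratio of 1.4 for the study group was used as the effect size". On the event rate, it says: "The overall probability that a participant would be diagnosed with an HPD was set at 15.9" percent. The result is given as: "The total number of subjects needed to achieve a power of 80% with a significance level of 0.05 was determined to be 1745".
- **Primary analysis (2.6.1, Objective 1.A).** "A Cox proportional hazards regression will be used to model the effect of using the digital platform plus RBPM" against the platform alone. Time runs from the first prenatal visit, and women never diagnosed are censored. Predicted survival curves and the median days to diagnosis per group will be shown.
- **Observation window (2.4).** For blood pressure readings: "All recorded values will be included from the first prenatal visit to 8 weeks postpartum for research objectives 1 and 2". No end of follow-up is given for HDP diagnosis itself.

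The article gives no expected number of days gained and no expected HDP risk per arm.

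**The concern.** 'Earlier' and 'more' are different effects, and the article itself separates them: more diagnoses for chronic hypertension, fewer days for HDP. A Cox hazard ratio mixes the two. When most women never have the event, moving a diagnosis forward by a few weeks hardly changes the risk sets, and the test mostly counts events. An effect size of 1.4 is then mainly a claim about how many women are diagnosed.

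Two errors become possible. A real gain of some weeks, with the same women diagnosed, would probably be reported as no effect. Additional coded diagnoses from more frequent readings, at unchanged times, would give a hazard ratio above 1 and be reported as shorter time to diagnosis. The planned median would not tell these cases apart, because a survival-curve median needs half of an arm to be diagnosed.

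**Working it through.** **1. Reproduce the plan's figure.** Inputs from 2.5: two-sided alpha 0.05, power 80%, 1:1 allocation, hazard ratio 1.4, event probability 0.159.

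Events = (1.960 + 0.842)² / (0.25 × ln(1.4)²) = 7.849 / 0.02830 = 277.3. N = 277.3 / 0.159 = 1744.1, rounded up to 1745. This matches exactly.

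**2. What the hazard ratio implies.** Under proportional hazards p1 = 1 − (1 − p0)^1.4, and (p0 + p1)/2 = 0.159. The solution is p0 = 13.5% and p1 = 18.3%. The difference is 4.9 points and the ratio 0.1833/0.1347 = 1.36. With 872.5 women per arm this is about 118 v 160 diagnoses.

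**3. How much of the 80% comes from the number diagnosed.** Compare the two proportions and ignore time. The standard error is √(2 × 0.159 × 0.841 / 872.5) = 0.0175, so z = 0.0486 / 0.0175 = 2.78 and power = Φ(2.78 − 1.96) = 79%. Timing adds almost nothing.

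**4. An extreme case that needs no timing curve.** Let 15.9% be diagnosed in each arm (138.7 women), with every RBPM diagnosis before any control diagnosis and nobody else leaving the risk set meanwhile.

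- Expected RBPM events while RBPM diagnoses occur: 138.7 − 872.5 × ln(1745/1606.3) = 66.5.
- Expected RBPM events while control diagnoses occur: 733.8 × ln(1606.3/1467.5) = 66.3.
- Observed minus expected = 138.7 − 66.5 − 66.3 = 6.0, with variance about 69.2.
- z = 6.0/√69.2 = 0.72; hazard ratio about exp(6.0/69.2) = 1.09; power about 11%.

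So even perfect separation in time comes nowhere near a hazard ratio of 1.4.

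**5. Realistic shifts, by simulation.** 4000 trials of 1745 per setting, with the same 15.9% diagnosed in each arm. Assumptions not in the article: first visit about 11 weeks (SD 4), diagnosis about 36.5 weeks (SD 4), delivery about 38.8 weeks (SD 2).

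| RBPM diagnoses earlier by | Cox power, follow-up to 8 weeks postpartum | Hazard ratio |
|---|---|---|
| 1 week | 5.5% | 1.01 |
| 2 weeks | 5.1% | 1.02 |
| 4 weeks | 5.4% | 1.04 |
| 8 weeks | 8% | 1.06 |
| 12 weeks | 10% | 1.08 |

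Other timing curves gave up to about 7% for 1 to 4 weeks. As a check on the method, a true proportional hazard ratio of 1.4 gave 79%.

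**6. Sensitivity** (shifts of 2 / 4 weeks unless stated).

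- 20% loss to follow-up: 5.6% / 8.0%.
- HDP risk 25%: 6.2% / 9.5%. HDP risk 30%: 6.9% / 12.8%. Section 2.5 says that prevalence at the site is above the national figure.
- Censoring at delivery, all diagnoses before delivery: 5.9% / 6.8%.
- Censoring at delivery, 5% of diagnoses otherwise postpartum, shifts of 1 to 4 weeks: 6–15%. With 15% postpartum: 17–41%. The highest value under another assumed curve was 69%. The gain arises mainly because the shift pulls postpartum diagnoses into the window. With 15% postpartum and a 4-week shift, 15.8% v 13.5% are counted as diagnosed.

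**7. The opposite error, and the limits of a timing measure.** In simulations of pure over-detection (13.5% v 18.3% diagnosed, identical timing among those diagnosed), the difference in restricted mean time lost to HDP was significant in about 62–65% of trials. That measure responds to timing far better than the Cox test. For 2 and 3 weeks earlier with postpartum follow-up, its power was about 46–72% and 76–96%, depending on the curve. By itself it still does not separate 'earlier' from 'more'.

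**8. The median.** At 13.5% and 18.3% diagnosed, neither survival curve falls to 50%.

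**The case against.** Cox regression is a conventional analysis for a time-to-event endpoint, the sample size arithmetic is right, and under a proportional hazard ratio of 1.4 more women have been diagnosed by every time point, which is one legitimate sense of 'sooner'. All of that stands.

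Three stronger readings are tempting and go too far.

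- *That the test measures more diagnoses and not earlier ones.* Timing does move the hazard ratio a little through the risk sets, to about 1.09 in the extreme case of step 4. 'Dominated by the number diagnosed' is accurate.
- *That the article assumes the same women are diagnosed in both arms.* It predicts fewer days and says nothing about cumulative HDP incidence. Closer monitoring could also record HDP that would otherwise be missed. Low power is therefore conditional on RBPM mainly advancing the same diagnoses.
- *That follow-up for HDP ends at 8 weeks postpartum.* Section 2.4 gives that window for blood pressure values. The end of follow-up for diagnosis may stand in a fuller plan, so its absence from an article is not in itself a fault. It matters here because it moves the power widely.

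Nor does it follow that the Cox test must be replaced. A restricted-mean primary analysis would cost roughly 10–15 points of power if hazards are proportional, requires choices about the truncation point and delivery, and does not by itself guard against over-detection.

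**Conclusion.** The concern holds as a mismatch between the stated hypothesis and the effect that the trial is powered for. The 80% is correct for an effect of about 13.5% v 18.3% diagnosed, and the article neither states nor justifies that increase. For a pure gain of 1 to 4 weeks in the same women, power is about 5–7% with follow-up to 8 weeks postpartum. With censoring at delivery it is roughly 6–69%, still below 80%.

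The implied proportions and the extreme case follow from the article's own inputs plus the conditions stated with them. The other power figures rest on assumed timing of first visit, diagnosis and delivery, and on an assumed postpartum share, so they are ranges and not predictions. The documents do not show that the 80% is miscalculated or that the trial cannot succeed. They show that a null result would not exclude a useful gain in time, and that a positive result would not establish one.

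**What to change.** **Section 2.5.** State that a hazard ratio of 1.4 with 15.9% overall implies about 13.5% v 18.3% diagnosed, give the reason for expecting that increase, and say that the 80% applies to that effect and not to a pure shift in timing. State the expected days gained and the power for that gain.

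**Section 2.6.1.**

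- Fix the end of follow-up for HDP diagnosis.
- Replace the median with two pre-specified key secondary results: the cumulative proportion diagnosed per arm by the end of follow-up, and a timing measure such as the difference in restricted mean time lost to HDP up to a fixed gestational age.
- Pre-specify the interpretation. Call a hazard ratio above 1 'earlier diagnosis' only when the timing measure favours RBPM and the cumulative proportions are similar. Otherwise report 'more diagnoses' or 'more and/or earlier'.

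Making the restricted-mean difference primary is optional, at the cost in power given above.

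**Cost.** Analysis wording, a revised and less favourable power statement, and a little more analysis. Section 2.4 already draws the timing of diagnosis and gestational age at delivery from the health record, so no new data are needed.

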##### Independent Variables and Covariates

The independent variable of interest will be a group variable. Participants will be randomized to one of two groups: the intervention group (digital platform with RBPM) or active comparison (digital platform, no RBPM). The covariates will be the age at enrollment in years, race, ethnicity, health insurance type (e.g., Medicaid, commercial, HMO), gestational age at first visit, and total number of prenatal visits. 

Demographic data will be summarized using means and standard deviations for continuous variables and frequencies and percentages for categorical variables. 

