##### Objective 1.B and Analysis Plan

The second analyses will be a binary variable for having, or not having, a new diagnosis of chronic hypertension during the prenatal period prior to 20 weeks of gestation. A logistic regression will be used to model the probability of being diagnosed with a new case of chronic hypertension during the prenatal period by study group. Regression coefficients with their respective *p*-values, and odds ratios with confidence intervals will be reported. 

#### 2.6.2. Research Objective 2

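### HDP already present at the first visit counts as a primary event that RBPM could not have affected, which dilutes the hazard ratio; the 1.B denominator has a related, smaller gap

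*Protocol article*

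**What the plan says.** All references are to the protocol article.

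- **Who enters (2.5).** "All people presenting at the study site for prenatal care will be invited to participate at their initial prenatal visit". The one stated exclusion is "Individuals younger than 18 years will be excluded". No limit is set on gestational age, existing HDP or known chronic hypertension.
- **When they are randomised (2.5).** "Randomization will occur at the time of enrollment, and baseline measures will be completed".
- **Primary event (2.6.1, Objective 1.A).** "an HDP is defined as gestational hypertension, preeclampsia, or preeclampsia with severe features".
- **Clock and censoring (Objective 1.A).** "The days to diagnosis of an HDP will be calculated from the date of the first prenatal visit to the date of diagnosis", and "A patient will be considered censored if they are never diagnosed with an HDP".
- **Analysis principle (2.3).** Phase 1 is a time-to-event analysis by intent to treat.
- **Covariates (2.6.1).** These include "gestational age at first visit, and total number of prenatal visits", so variation in gestational age at entry is expected.
- **Objective 1.B (2.6.1).** The outcome is "having, or not having, a new diagnosis of chronic hypertension during the prenatal period prior to 20 weeks of gestation", modelled by logistic regression on study group. Coefficients, p-values and odds ratios with confidence intervals are to be reported. No denominator is defined. The matching hypothesis in 2.3 concerns chronic hypertension that had not been recognised before.

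**The concern.** Each rule is reasonable alone; the difficulty lies in their combination. A woman whose first visit is late in pregnancy, and whose HDP is recognised at that visit, is eligible, is randomised and is scored as an event at about day 0. Home monitoring had no chance to bring that diagnosis forward, yet it carries the same weight in the Cox model as one made weeks later. Adjusting for gestational age at first visit does not help, because the event precedes any use of the intervention.

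Randomisation spreads these women evenly on average. What is at stake is therefore a hazard ratio pulled towards 1 and lost power in the primary analysis.

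Objective 1.B has a related gap. A woman first seen at 20 weeks or later, or with chronic hypertension already on record, cannot have the outcome but is counted as not having it. A new diagnosis made at the entry visit itself counts as an outcome although RBPM could not have produced it.

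**Working it through.** **Inputs (2.5):** hazard ratio 1.4, 1:1 allocation, two-sided alpha 0.05, power 80%, event probability 15.9%, N = 1745.

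**Step 1: reproduce the plan's figure.** Schoenfeld's formula gives

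D = (1.960 + 0.842)² / (0.25 × (ln 1.4)²) = 277.3 events,

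N = 277.3 / 0.159 = 1744.1, rounded up to 1745.

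This matches, so the arithmetic is not at fault. The calculation does treat every one of the 15.9% as an event RBPM can affect. That figure is the share of US delivery hospitalisations affected by HDP, so it is not an incidence after enrolment.

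**Step 2: allow for events at entry.** Let f be the share of all HDP events already present at entry. The documents do not give f; 5%, 10% and 15% are assumptions. Expected events at N = 1745 are E = 1745 × 0.159 = 277.5.

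- *Counted:* the entry events carry no treatment effect, so log HR = (1 − f) × ln 1.4 on E events.
- *Removed:* log HR = ln 1.4 on E × (1 − f) events.
- *Power* = Φ(log HR × √events / 2 − 1.96).

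Example at f = 10%:

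- Counted: 0.9 × 0.3365 × √277.5 / 2 − 1.96 = 0.56, so power is 71%.
- Removed: 0.3365 × √249.7 / 2 − 1.96 = 0.70, so power is 76%.

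| f (assumed) | Events at entry | Share of 1745 women | HR if counted | Power, counted | Power, removed | N for 80%, counted | N for 80%, removed |
|---|---|---|---|---|---|---|---|
| 5% | 13.9 | 0.8% | 1.38 | 75.9% | 78.0% | 1933 | 1836 |
| 10% | 27.7 | 1.6% | 1.35 | 71.3% | 75.8% | 2154 | 1938 |
| 15% | 41.6 | 2.4% | 1.33 | 66.3% | 73.4% | 2414 | 2052 |

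The stated volume and enrolment rate give about 0.60 × 3000 = 1800 women, so there is little slack at a 15.9% rate.

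**Step 3: the offset.** Section 2.5 says HDP is more common at the site than 15.9%, without a figure. The overall rate that restores 80% power at N = 1745 is 15.9% / (1 − f) with entry events removed, and 15.9% / (1 − f)² with them counted:

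- f = 5%: 16.7% removed, 17.6% counted
- f = 10%: 17.7% removed, 19.6% counted
- f = 15%: 18.7% removed, 22.0% counted

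A higher rate can restore power. It does not restore the hazard ratio while entry events are counted.

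**Step 4: Objective 1.B.** Suppose, for illustration only, risks of 3% and 5% among women who can have the outcome.

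- All can have it: OR = (0.05/0.95) / (0.03/0.97) = 1.70.
- 20% cannot (2.4% v 4.0%): OR = (0.04/0.96) / (0.024/0.976) = 1.69.
- 40% cannot (1.8% v 3.0%): OR = (0.03/0.97) / (0.018/0.982) = 1.69.

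Women who cannot have the outcome hardly move the odds ratio. Entry-visit diagnoses act differently: they add equally to both arms' outcomes and so pull the odds ratio towards 1. The documents give no basis for sizing that.

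**The case against.** The strongest reply is that enrolling all comers and analysing by intent to treat is a legitimate pragmatic choice, and that a condensed article may leave at-risk sets to the full protocol or analysis plan. Enrolment at the initial visit, with surveys each trimester, suggests that most women enter early, so f may be at or below the low end. Dilution is conservative. Removing entry events recovers only about 2 power points at f = 5% and about 5 at f = 10%, and the site's higher rate may cover some of the loss.

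Most of this stands, and it limits the size of the point. It does not remove it. The article states the population, time origin, event and censoring rule, and together these count the entry events.

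Several stronger readings are tempting but not supported:

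- **Bias between the arms.** Entry status precedes randomisation and is balanced on average.
- **Negative survival times for women transferring in with HDP already coded.** This depends on whether the first prenatal visit means the first at this site or the first anywhere, and the article does not say.
- **A misreported absolute difference in 1.B.** The plan lists odds ratios for this objective, and no risk difference or predicted probability.
- **A large known share of site patients with chronic hypertension.** The Introduction gives only higher odds for Black than for white women, with no share for this site.
- **Everyone is enrolled.** Everyone is invited, and 60% are expected to enrol.

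**Conclusion.** The point holds as one of dilution. As written, an HDP present at entry is a primary event that RBPM could not have influenced. If 5–15% of the planned events were of this kind, the expected hazard ratio would fall from 1.40 to about 1.38–1.33. Power would be about 76–66% with them counted, against 78–73% with them removed. These figures rest on an assumed share, no treatment effect on entry events, and the planned 15.9% event rate; a higher site rate would make the power loss smaller.

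For 1.B the gap is mainly one of definition. The modelled probability is not that of women in whom hypertension could be newly found, and entry-visit diagnoses dilute the comparison. Women who cannot have the outcome change the odds ratio little.

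This should be corrected because the remedy is cheap, but it does not invalidate the randomised comparison.

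**What to change.** In 2.6.1:

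- **Objective 1.A.** Define the analysis set, from pre-randomisation data only, as women with no HDP diagnosis dated on or before the day of randomisation. Apply the rule identically in both arms.
- **Objective 1.B.** Restrict the denominator to women randomised before 20 weeks with no chronic hypertension on record at entry, and count only diagnoses made after randomisation.
- **Secondary outcomes.** Keep all randomised women. Excluding them from randomisation would needlessly drop them from the perceived-quality, stress and severe-morbidity analyses in 2.4.

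Because both sets depend only on status at entry, the intent-to-treat comparison within them is preserved. Section 2.7 says prior diagnoses and chronic conditions are held as structured EHR data, so no new data collection is needed.

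The cost is a slightly smaller analysed number, made up of women who carry little or no information on the effect. Removal does not by itself bring power back to 80% at N = 1745 and a 15.9% rate, so the event probability in 2.5 is best restated as incidence after entry in the 1.A set. The definitions should be fixed before outcome data by arm are seen.
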